**8-2 Exclusion Criteria**

(1) Intraepithelial carcinoma

(2) Stage IV

(3) The patient who underwent the sentinel node biopsy only

(4) The patient who underwent the total mastectomy and the simultaneous reconstruction surgery

(5) When the shoulder movement disorder derived from the other preoperative shoulder-related diseases exists.

(6) The patient with a breast cancer on the east side or the history of surgery on the axillaries

(7) The patient who is pregnant or breastfeeding

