**10.3 Methods of Clinical Trial**

(1) Clinical Trial Design

The eligibility evaluation is conducted with the subject who underwent the modified radical mastectomy or breast preservation surgery and the axillary lymph node dissection at Asan medical center and signed at the consent form voluntarily subsequent to the screening test. The subject who isn’t included in the exclusion criteria visits the hospital on the operation day and undergoes the modified radical mastectomy or breast preservation surgery and the axillary lymph node dissection. Then, the subject is assigned to the investigational group or control according to the random assignment slip.

 EG: Guardix SG

 CG: Not applicable

That means the investigational device will be or won’t be applied onto the surgical site of subject depending on her group. Since the investigational device is applied inside of subject in the middle of surgery under anesthetic, the subject is unaware of treatment’s detail.

The related tests will be performed on the 7th, 3, 6 and 12 months subsequent to the surgery. In addition, the double-blind policy is maintained since the application of investigational device is performed by the expert who has a medical expertise and technique on the surgery and the application of investigational device, and the evaluator couldn’t know about the rule of random assignment and the allocation of subject to the group since the evaluator isn’t involved to the application of investigational device.

(2) Random Assignment of Subjects

In this clinical trial, random assignment was used to reduce bias that could be involved in the assignment of EG and CG, and to enhance the effects of comparison. To compare the precise difference in the range of motion of patient who underwent the partial mastectomy or total mastectomy, the subjects are assigned to each group randomly in similar proportion.

Our random assignment method is the block random assignment performed after generating random numbers (upto 4 places of decimals) for each subject using Excel’s random function (RAND). The sealed assignment slip is distributed to the subject. The sponsor of clinical trial provides the blinded slip which the investigational group or control is written down according to the randomly assigned subject table.

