Subject numbers were given by each clinical trial institution, and the institution assigned a screening number to each subject who signed the written consent and completed the screening test. Upon completion of the screening process, and if a subject was recognized to be appropriate for this study, a random assignment number was given in sequence, then treated with the investigational device.

The screening number as well as the random assignment number of a dropout subject was also dropped out. A new subject must be provided with a new subject screening number and random assignment number.

(3) Code Breaking

The blindness must not be disclosed during the clinical trial period in any case. The blindness can only be disclosed if the subjects are in emergency situation, and the group they belong to is absolutely required to be identified. In this case, the blindness can be disclosed according to the appropriate process, and details must be recorded in written documents.

(4) The method of surgery and the application method of medical device

Subsequent to surgery, the 3ml(injection volume) of Guardix SG is applied to the subject who underwent the modified radical mastectomy or breast preservation surgery and the axillary lymph node dissection, the standard surgery method to treat the breast cancer.

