**11-4 Timeline of exam and schedule**

The subject will participate in the clinical trial after being approved as the suitable subject who isn’t included in the exclusion/inclusion criteria through the screening test and assigned to the control and the investigational group randomly.

The observation items to be checked during each visit according to the study timeline are as follows.

Clinical trial Schedule

| Items | Treatment and Observation Period | | | | | |
| --- | --- | --- | --- | --- | --- | --- |
| No. of Visits | ^Visit 1^ | ^Visit 21^ | | Visit 3 | Visit 4 | Visit 5 |
|  | Before surgery | Immediately after surgery | 7 days after surgery | 3 month after surgery | 6 months after surgery | 12 months after surgery |
| Visit Window (Day) |  |  | ± 2 | ± 14 | ± 14 | ± 30 |
| Inclusion/ Exclusion Criteria | ○ |  |  |  |  |  |
| Informed Consent | ○ |  |  |  |  |  |
| Basic Information and Medical History | ○ |  |  |  |  |  |
| Hematologic Tests^2^ | ○ |  | ○ |  |  |  |
| Measurement of drainage volume³ |  | ○ | ○ |  |  |  |
| Analysis of body composition | ○ |  |  | ○ | ○ | ○ |
| Investigational medical device prescription |  | ○ |  |  |  |  |
| Measurement in the range of shoulder joint’s motion | ○ |  |  | ○ | ○ | ○ |
| Evaluation on the upper limbs’ locomotive capacity | ○ |  |  | ○ | ○ | ○ |
| Evaluation of pain | ○ |  |  | ○ | ○ | ○ |
| Evaluation of Adverse Events |  |  | ○ | ○ | ○ | ○ |

1) The test for blood and the adverse events scheduled on the visit 2 will be evaluated based on the adverse events discovered on the discharge date of patient or on the 7th day subsequent to the surgery by revisiting the patient.

2) Hematologic Tests - WBC, Neutrophil

The blood test to be performed on the 7th day subsequent to surgery will be conducted only if the adverse events such as the flare onto the surgical site or the fever exists following the surgery. The intention of above-mentioned test (test item: CBC, CRP, and etc.) is to check whether the inflammation factor is increased and the number of white blood cell within 7 days from the surgery.

3) Measurement of drainage volume - Shall be measured at an interval of two days until the 7th day from the surgery date and complete the measurement of it on the discharge date from hospital.

① Visit 1 (Screening visit)

 Written consent signed by subjects

 Investigation on the basic information about the subject, medical history and previous medical history related to shoulder joint

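### Random assignment is placed both at or after the operation and on completion of preoperative screening, although eligibility can be finally confirmed only by the operation performed

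*Protocol*

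**What the plan says.** **Assignment at or after the operation.** In Protocol 10.3 (1), an eligible subject "visits the hospital on the operation day and undergoes the modified radical mastectomy or breast preservation surgery and the axillary lymph node dissection". The next sentence reads "Then, the subject is assigned to the investigational group or control according to the random assignment slip". The Visit 2 list in 11-4, which runs from the operation to day 7, agrees: it enters randomisation together with application of the device. The Visit 1 list has no randomisation entry.

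**Assignment on completion of screening.** In 10.3 (2), once screening is finished and the subject is judged suitable, "a random assignment number was given in sequence, then treated with the investigational device". The opening sentence of 11-4 has subjects approved "through the screening test and assigned to the control and the investigational group randomly", with no mention of the operation. Section 11-4 labels Visit 1 as the screening visit, and both copies of the schedule head it as before surgery.

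**Eligibility.** Inclusion 3 (8-1) requires mastectomy or breast preservation surgery with axillary dissection, worded as already performed. Exclusion 3 (8-2) is "The patient who underwent the sentinel node biopsy only", and exclusion 4 is total mastectomy with simultaneous reconstruction. Both schedules mark the criteria at Visit 1 only. Section 11-1 (3) bases the check on consent, demography, history and preoperative histology.

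**Slip and blinding.** Section 10.3 (2) says "The sealed assignment slip is distributed to the subject". The title claims blinding of subject and assessor, not of the operator.

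**The concern.** The moment of allocation decides who belongs to the randomised comparison. Where eligibility rests on what was done in the operation, allocating beforehand brings in patients who may then prove ineligible, for example because only a sentinel biopsy was performed. Removing them later is an exclusion after randomisation, and it is free of bias only if the decision cannot depend on the arm. The protocol offers no such assurance, because it does not fix when the slip is opened and does not blind the operator.

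The statement that the slip goes to the subject adds a second difficulty. DASH and VAS are self-reported, and the primary measure is active range of motion, which depends on the subject's effort. Section 10.3 (1) rests subject blinding on the device being applied under anaesthetic, so any route by which the subject could learn the arm should be closed.

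**Working it through.** **1. The four statements on timing, side by side**

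| Place | Time of assignment |
| --- | --- |
| 10.3 (1) | after the operation, by slip |
| 11-4, Visit 2 list | Visit 2, with device application |
| 10.3 (2) | on completion of screening |
| 11-4, opening sentence | after approval at screening |

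Two places support each time. The sentence in 10.3 (2) begins "Upon completion of the screening process, and if a subject was recognized to be appropriate for this study, a random assignment number was given in"; it names no later event on which the number waits. The word preoperative is not in that sentence; it comes from the schedule, where screening is Visit 1. The moment of application is itself stated in two ways: during the operation in 10.3 (1) and after it in 10.3 (4). Those passages also need to be reconciled.

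**2. Is there an eligibility check between operation and allocation?** None is scheduled. The criteria are marked at Visit 1 only, and the Visit 2 list holds randomisation but no eligibility item.

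**3. What happens to a patient randomised at screening and found ineligible at surgery?**

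- Section 13-3 defines registration as random assignment, and 13-4 (3) allows discontinuation for breach of the inclusion criteria.
- Section 15-3 (5) keeps serious protocol deviators in the ITT analysis and removes them from the PP analysis.
- The same section limits ITT to subjects who used the device at least once after assignment. A patient allocated to the device but left untreated therefore falls outside ITT.
- Controls receive nothing (10.2 and 10.3 (1)), so the device-use condition cannot be applied to both arms alike.

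**4. Size, as an illustration only**

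The plan's own figure comes first. Inputs from 8-3: SD 10, one-sided alpha 0.025, power 90%, 1:1 allocation, and a distance between assumed difference and margin of 5 degrees (for example 15 − 10).

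- Normal approximation: n = 2 × (1.960 + 1.282)² × 10² / 5² ≈ 84.1, so 85 per group.
- Noncentral t, with noncentrality 5 / (10 × √(2/n)): power is 0.8999 at n = 85 and 0.9032 at n = 86. The stated 86 per group and 0.90323 are reproduced.
- Dropout: 86 / 0.9 = 95.6, so 96 per group and 192 in total, as stated.

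Now let x be the share of randomised patients found ineligible at surgery. The documents give no value, so x is an assumption. Evaluable per group = 96 × (1 − x) × 0.9, rounded down. Enrolment that restores 86 = 86 / (0.9 × (1 − x)), rounded up.

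| x | Excluded of 192 | Evaluable per group | Power | Enrolment per group to restore 86 |
| --- | --- | --- | --- | --- |
| 0% | 0 | 86 | 0.903 | 96 |
| 5% | about 10 | 82 | 0.889 | 101 |
| 10% | about 19 | 77 | 0.869 | 107 |
| 20% | about 38 | 69 | 0.831 | 120 |

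**The case against.** The best defence is that the inconsistency is one of wording. The two explicit time statements, 10.3 (1) and the Visit 2 list, agree with each other. The other two can be read as order and not clock time: screening comes first, then assignment. In 10.3 (2) the number and the treatment stand next to each other, which fits allocation in theatre. A sequential number need not reveal the arm while the slip is sealed. The title and 8-3 speak of patients scheduled for the surgery, so eligibility by planned operation is a natural reading, and the past tense in this text is unreliable. Section 15-3 keeps serious deviators in ITT.

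Much of this stands, and it limits what may be inferred. Three stronger readings are tempting, and the documents do not support them:

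- *The surgeon knows the arm while operating.* No section says the slip is opened before the dissection ends. The text only fails to rule it out.
- *The slip unblinds the subject.* The phrase may mean one slip allotted per subject. Nothing says the subject opens or reads it. The wording is ambiguous and sits badly with subject blinding, but it does not show unblinding.
- *The operation-based criteria are unknown until theatre.* That is too strong for planned procedures. What holds is that they can be finally confirmed only by the operation performed.

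The defence does not remove the conflict. A reader who follows 10.3 (2) would issue the number at the end of a preoperative visit. The protection from ITT is incomplete, because the same section makes membership depend on device use.

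**Conclusion.** The point holds as an inconsistency to resolve before the protocol is used: the time of random assignment is stated in two incompatible ways, operation-based eligibility is checked only before surgery, and the opening of the slip is not fixed. If the screening-time reading is followed, exclusions after randomisation become possible and the ITT definition does not repair them.

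A reader might take the fall in power to between 88.9% and 83.1% as an estimate of the damage. It is not: it rests wholly on the assumed 5% to 20% of patients found ineligible at surgery, and every value stays above the 80% listed in 15-3 (4), though below the 90% planned in 8-3. The real stake is possible selection after randomisation and weak concealment. Neither can be quantified from the documents, and neither is shown to have occurred.

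**What to change.** - Reword 10.3 (2) and the opening sentence of 11-4 to match 10.3 (1) and the Visit 2 list, so that one point of allocation is stated throughout.
- Add an eligibility confirmation to Visit 2 in both schedules, made before allocation: axillary dissection was done, without simultaneous reconstruction.
- State that theatre staff hold the sealed slips, open the next one in sequence only after that confirmation, and never give it to the subject or the evaluator. Delete the statement that the slip is distributed to the subject.

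The cost is wording in 10.3 and 11-4, one eligibility tick at Visit 2, and slips at hand in theatre. The sample size need not change, since patients found ineligible at surgery would then never be randomised.

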**11. Monitoring Items and Monitoring Methods**

**11-1 Monitoring Items and Methods**

(1) Information Consent and Demographical Data

Before participating in the clinical trial, the purpose and procedure of clinical trial are explained to subject in detail and demographical information such as the receipt of the written consent and date, subjects’ initials, height, and BMI is recorded in the CRF. The copy of informed consent form is provided to the subject after receiving the written consent from subject.

(2) Past History and Physical function

The subject will be informed about the clinical trial continually. We recorded the stage of disease, medical history, the info related to the predisposing conditions on the shoulder joint, blood test, the range of shoulder joint’s motion, the evaluation on the exercise capability of upper limbs, and the evaluation on pain derived from the movement.

(3) Subject Eligibility Evaluation (Inclusion/Exclusion Criteria checking)

recorded the result conducted after evaluating whether the suitable subject is selected according to the inclusion/exclusion criteria based on the consent for the participation of clinical trial, demographical survey, medical history, the preoperative histological diagnosis, and etc.

(4) Observation items related to the surgery

- Basic information on the surgery

Operation date, Name of surgery, histopathological diagnosis, TNM stage, postoperative therapy (cancer chemotherapy, anti-hormone therapy, target therapy, radiotherapy)

- Safety evaluation

Adverse events (complication discovered during the hospitalization and surgery-related complication), Measurement of drainage volume subsequent to surgery, Observation of infectious symptom, Complete blood count exam (POD#7)

(5) Physical function (Before surgery, after surgery 3, 6, 12 months)

- Efficacy evaluation

Shoulder range of motion (Abduction, Horizontal abduction, Flexion, External rotation), Evaluation on the upper limbs’ locomotive capacity, the evaluation on pain derived from the movement, Evaluation on the lymphedema using the analysis of body composition

**11-2 Assessment of Efficacy Criteria and method [6], [8], [9], [12], [13], [17], [23], [24], [25], [26], [27]**

1. Shoulder range of motion

The Shoulder ROM (name of equipment) which measures 4 kinds of active range of motion using the universal full-circle manual goniometer is used for measurement.

[figure not shown]

**<Shoulder flexion>**

The movement of abduction and flexion are measured at the coronal, scapular plane and sagittal planes in the neutral anatomical position.

[figure not shown]

**<Abduction>**

[figure not shown]

**<External rotation>**

The movement of external rotation is measured with his/her shoulders abducted at 90° degrees, elbows flexed at 90° degree, forearms pronated in the lying and standing position. When measuring in standing position, the patient’s forearms shall be placed to the floor horizontally and his/her palms shall be directed toward the floor.

[figure not shown]

**<Horizontal abduction>**

With his/her shoulders abducted at 90° degree and elbows flexed at 90° degrees, the fully abducted angle shall be measured at the horizontal plane.

(2) Evaluation on the upper limbs’ locomotive capacity (Questionnaire – DASH)

** Refer to the attached

(3) The evaluation on pain derived from the movement

The subject selects the pain level within the diagram designed using VAS (visual analogue scale is the verified assessment tool., 0 means the absence of pain and 100 means the worst pain) stated in the questionnaire, and the examiner records the distance between the starting point and the ending point after measuring it using the ruler at the case report form.

** Refer to the attached

(4) Evaluation on the lymphedema using the analysis of body composition

After analyzing the body composition using Inbody S10(Body composition analyzer), evaluate the degree of arm’s lymphedema which occurred near the operated breast.

**11-3 Assessment of Safety Criteria and method**

(1) Laboratory Tests

Hematologic Tests – WBC, Neutrophil

(2) Evaluation of Adverse Events

Investigators shall educate the subject to report the adverse events voluntarily and occasionally and check the adverse events which occurs in the subject by interviewing or reviewing the report kept in hospital during the visit.

(3) The evaluation on pain derived from the movement

(4) Drainage volume subsequent to the surgery

Drainage volume (ml) unit shall be surveyed.

(5) Expected Adverse Events

In case of the infection which occurs as an adverse events following the use of investigational medical device, we confirmed its degree by checking up the clinical sign and performing the blood test (the white blood cell count (WBC)) scheduled to 7th following the surgery.
In case of the allergic reactions (generalized eruption, respiratory dyspnea, edema, pain, and inflammation), we analyzed the causal relationship with the usage of investigational device by checking up the clinical signs.

**11-4 Timeline of exam and schedule**

The subject will participate in the clinical trial after being approved as the suitable subject who isn’t included in the exclusion/inclusion criteria through the screening test and assigned to the control and the investigational group randomly.

The observation items to be checked during each visit according to the study timeline are as follows.

Clinical trial Schedule

| Items | Treatment and Observation Period | | | | | |
| --- | --- | --- | --- | --- | --- | --- |
| No. of Visits | ^Visit 1^ | ^Visit 21^ | | Visit 3 | Visit 4 | Visit 5 |
|  | Before surgery | Immediately after surgery | 7 days after surgery | 3 month after surgery | 6 months after surgery | 12 months after surgery |
| Visit Window (Day) |  |  | ± 2 | ± 14 | ± 14 | ± 30 |
| Inclusion/ Exclusion Criteria | ○ |  |  |  |  |  |
| Informed Consent | ○ |  |  |  |  |  |
| Basic Information and Medical History | ○ |  |  |  |  |  |
| Hematologic Tests^2^ | ○ |  | ○ |  |  |  |
| Measurement of drainage volume³ |  | ○ | ○ |  |  |  |
| Analysis of body composition | ○ |  |  | ○ | ○ | ○ |
| Investigational medical device prescription |  | ○ |  |  |  |  |
| Measurement in the range of shoulder joint’s motion | ○ |  |  | ○ | ○ | ○ |
| Evaluation on the upper limbs’ locomotive capacity | ○ |  |  | ○ | ○ | ○ |
| Evaluation of pain | ○ |  |  | ○ | ○ | ○ |
| Evaluation of Adverse Events |  |  | ○ | ○ | ○ | ○ |

1) The test for blood and the adverse events scheduled on the visit 2 will be evaluated based on the adverse events discovered on the discharge date of patient or on the 7th day subsequent to the surgery by revisiting the patient.

2) Hematologic Tests - WBC, Neutrophil

The blood test to be performed on the 7th day subsequent to surgery will be conducted only if the adverse events such as the flare onto the surgical site or the fever exists following the surgery. The intention of above-mentioned test (test item: CBC, CRP, and etc.) is to check whether the inflammation factor is increased and the number of white blood cell within 7 days from the surgery.

3) Measurement of drainage volume - Shall be measured at an interval of two days until the 7th day from the surgery date and complete the measurement of it on the discharge date from hospital.

① Visit 1 (Screening visit)

 Written consent signed by subjects

 Investigation on the basic information about the subject, medical history and previous medical history related to shoulder joint

 Preoperative histological diagnosis

 Laboratory Tests were conducted

 Physical function (Shoulder range of motion: Abduction, Horizontal abduction, Flexion, External rotation), Evaluation on the upper limbs’ locomotive capacity, the evaluation on pain derived from the movement

 The analysis of body composition

 Evaluation on the subject eligibility for this clinical trial

② Visit 2(OPD~POD #7)

 The investigational device was applied (The EG, The CG Randomization)

 Histopathological diagnosis and TNM stage

 Postoperative adjunctive therapy (cancer chemotherapy, anti-hormone therapy, target therapy, radiotherapy)

 Postoperative total capacity

 Laboratory Tests were conducted (POD #7)

 Evaluation of Adverse Events

③ Visit 3, 4, 5(POD 3, 6, 12 months)

 Physical function (Shoulder range of motion: Abduction, Horizontal abduction, Flexion, External rotation), Evaluation on the upper limbs’ locomotive capacity, the evaluation on pain derived from the movement

 The analysis of body composition

 Evaluation of Adverse Events

